#### 2.3.1. Control Group Treatment

Patients undergoing neoadjuvant treatment for LARC with a major clinical response at restaging will undergo a local excision 16 (±1) weeks after the end of neoadjuvant therapy and histopathological examination with TRG evaluation. Local excision can be performed either with the conventional technique (TAE), or the Transanal endoscopic microsurgery (TEM) or other techniques (TAMIS), provided that the following principles are respected: free macroscopic margin of at least 0.5 cm, full thickness excision, fixation of the operative piece on support to facilitate the histological interpretation of the pathologist.

After histopathological examination, based on pathological findings, Total Mesorectal Excision (TME) can then be planned for the patients if, as expected from clinical practice, ypT ≥ 2, there is the presence of positive margins, TRG > 2 and the cancer is poorly differentiated (G3).

#### 2.3.2. Experimental Group Treatment

In the treatment arm, patients undergoing neoadjuvant treatment for LARC with major clinical response at restaging will undergo Electrochemotherapy (ECT) 12 (±1) weeks after the end of neoadjuvant therapy. After four weeks (±5 days) of ECT, the patients will undergo a surgical treatment with local excision and histopathological examination with TRG evaluation.

After histopathological examination, based on pathological findings, TME can be planned for the patients.

Patients will receive Bleomycin intravenously (15,000 IU BLM/m^2^) and after 8 min, an electric pulse delivered to the lesion will be performed with the CLINIPORATOR™ (IGEA Ltd., Modena, Italy) with the insertion of appropriate CE certificate electrodes for endoluminal treatment [4]. The procedure must be completed within 40 min from the end of the bleomycin injection. The anesthesia will be induced after bleomycin injection and before the application of the electrodes in the case of local anesthesia, or before bleomycin injection in the case of general anesthesia.

### 2.4. Duration of the Study and Follow up

The study will last 36 months with five follow-up years for all patients enrolled. The time for enrolment will be 36 months.

Patients after local excision will be visited every three months in the first two years, and then every six months in the following three years.

This study is subject to stopping rules. Patients can decide to interrupt the treatment. Subjects who discontinue/withdraw from study participation will be evaluated by study personnel.

Starting from the informed consent signature, any event occurring during the treatment phase and/or the follow up phase, will be considered an Adverse Event (AE) and will be recorded. Any clinical or biological abnormalities not present at the trial start will be considered intercurrent events.

The visits scheme is summarized in Table 2.

### 2.5. Description of Study Procedures

Quality of life (QoL), as measured by the EQ5d questionnaire, will be completed at Visits 1, 2, 3, 5, 6, 7, 8, 9, 10, 11 and 12 and will be considered optional from visit 13 to 18. The EQ-5D was developed in Europe and it is a descriptive system of preference-based Health Related Quality Life [30]. The EQ-5D questionnaire also includes a VAS, by which respondents can report their perceived health status with a grade ranging from 0 (the worst possible health status) to 100 (the best possible health status). Pain will be assessed at Visits 1, 2, 3, 5, 6, 7, 8, 9, 10, 11 and 12.

#### 2.5.1. Visit 1

All patients will undergo the same enrollment/baseline visit (Visit 1) procedures. Clinical examination will include the measurement of weight, height and vital signs (pulse, blood pressure). Patients must sign the informed consent form. The Screening/Enrollment Visit (Visit 1) procedures must be performed not more than 12 (±1) weeks after the end of neoadjuvant therapy. Patients who fulfill all inclusion criteria will be enrolled. Patients who are Eastern Cooperative Oncology Group ECOG (ECOG) Performance Status grade 0, 1 or 2 are eligible for study participation [31].

Study procedures at Visit 1 consist of the following: screening against inclusion/exclusion; randomization to ECT or standard treatment; and Complete Blood Count (CBC) and coagulation profiles evaluation. An absolute neutrophil count below 1000/mL, a platelet count below 70,000/mL, and/or an international normalized ratio (INR) above 1.5 will be considered exclusion criteria. The patients will be subjected to rectal exploration; rectoscopy; routine hematochemistry and carcinoembryonic antigen (CEA), Magnetic Resonance (MR) with contrast medium (cm) and Computed Tomography (CT) with contrast medium. Medical and Oncology history, including any previous treatments, concomitant treatments, medications, and events will be registered. Pain will be evaluated according to the Visual Analog Scale (VAS) scale and Quality of Life will be monitored according to the EQ5d questionnaire.

All patients will undergo a pre-anesthetic visit and will be excluded from study participation if not eligible for general anesthesia or monitored anesthesia care (conscious sedation).

The major clinical response after neoadjuvant treatment will be evaluated 12 weeks from the end of radiotherapy with the following tests: laboratory exams, CEA dosage, CT of chest and abdomen with contrast medium, MR pelvis with contrast medium and rigid rectoscopy. The major clinical response is classified as the absence of palpable mass to the digital exploration of the rectum and pathological lymph nodes (>5 mm of diameter along the short axis) to the pelvic MRI, and the absence of deep or superficial ulcers > 2 cm of diameter, at rectoscopy.

#### 2.5.2. Visit 2

The patients with confirmed eligibility will be treated with ECT. The type of anesthesia will be determined by the anesthesiologist. The patients will undergo clinical evaluation, pain assessment by VAS score and blood samples and CEA dosage. The use of concomitant treatment or drug for pain control will be registered.

#### 2.5.3. Visit 3

At day 30 ± 3 (Visit 3), all patients randomized in the control or treatment group will be subjected to LE according to established clinical and institutional practices. The patients will undergo the same procedures as above and according to timing reported in Table 2: Evaluation of routine hematochemistry and CEA, pain assessment by VAS scale and Quality of Life (life quality evaluation according to EQ5d questionnaire) will be completed.

#### 2.5.4. Visit 4

The patients will undergo histological examination; surgical specimens containing the tumor will be evaluated and scored according to TRG, as proposed by Mandard et al. [28], by an expert pathologist who is not aware of the clinical and diagnostic findings. Adverse events/complication will be recorded. Pain evaluation and QoL will be assessed.

#### 2.5.5. Visit 5, 7, 9, 11

After clinical evaluation, the patients will be submitted to rectoscopy, colonoscopy, pain assessment by VAS score and blood samples and CEA dosage. The use of concomitant treatment or drugs for pain control will be recorded. Adverse events/complication will be noted.

#### 2.5.6. Visit 6, 10, 13, 15, 17

After clinical evaluation, the patients will be submitted to rectoscopy, colonoscopy, MRI, pain assessment, blood samples and CEA dosage as above. The use of concomitant treatment or drugs for pain control will be recorded. Adverse events/complication will be noted.

#### 2.5.7. Visit 8, 12, 14, 16, 18

After clinical evaluation, the patients will be submitted to rectoscopy, colonoscopy, CT, MRI, clinical evaluation, pain assessment, blood samples and CEA dosage as above. The use of concomitant treatment or drugs for pain control will be recorded. Adverse events/complication will be noted.

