## Figures and Tables

**Figure 1 cancers-13-03199-f001:**
[figure not shown]
Trial design flowchart.

**Table 1 cancers-13-03199-t001:** Inclusion and Exclusion Criteria.

Inclusion Criteria	Exclusion Criteria
Patients of both sex aged ≥18 years	Age less than 18 years
Histological confirmation of rectal adenocarcinoma	Patients with neoplasia more than 12 cm from the anal margin
Patients undergoing neoadjuvant treatment for locally advanced tumor of the rectum with confirmed major clinical response after neoadjuvant treatment	Patients with stable disease or disease progression after neoadjuvant treatment
Rectal tumor up to 12 cm from the external anal margin	Patients who, for medical reasons, cannot be given bleomycin
Patients must be willing to comply with the study protocol and give their informed written consent	Lesions unsuitable for Electrochemotherapy (ECT) (bony invasion, large vessels infiltration, etc.)
Patients with an Eastern Cooperative Oncology Group (ECOG) status performance <3	Acute lung infection
	Poor lung function symptoms
	Severe coagulation disorders
	Previous allergic reactions to bleomycin
	Previous cumulative bleomycin dose over than 250 mg/m^2^
	Chronic renal dysfunction (creatinine> 150 µmol/L)
	Pregnancy or lactation

**Table 2 cancers-13-03199-t002:** Visits Scheme.

Visit #		1	2	3	4	5	6	7	8	9
**Time**		Month −1 (up to 1 month prior the treatment)	Day 0 ± 3 days	Day 30 ± 3 days	Day 37 ± 3 days	12 ± 1 week	24 weeks ± 1 week	36 ± 1 week	48 ± 1 week	60± 1 week
	**Visit Description**	Restaging, enrolment, randomization	Treatment group: Electrochemotherapy	Local Excision	Histological examination	Follow up visit	Follow up visit	Follow up visit	Follow up visit	Follow up visit

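### The neutrophil and platelet exclusion limits in section 2.5.1 are printed per mL, 1000-fold below the same numbers per microlitre; most likely a unit slip

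*Protocol article*

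**What the plan says.** Section 2.5.1 of the protocol article lists the Visit 1 procedures, among them a complete blood count and a coagulation profile, and attaches numeric limits to the results. For the counts it states: "An absolute neutrophil count below 1000/mL, a platelet count below 70,000/mL". The same sentence adds the clotting limit and makes all three binding: "an international normalized ratio (INR) above 1.5 will be considered exclusion criteria".

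Three other places bear on the point:

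- Still in section 2.5.1, every patient has a pre-anesthetic visit, and patients "will be excluded from study participation if not eligible for general anesthesia or monitored anesthesia care".
- Section 2.5.2 (Visit 2) gives the consequence of passing the screen: "The patients with confirmed eligibility will be treated with ECT". Section 2.3.2 describes that treatment as intravenous bleomycin followed by electric pulses through inserted endoluminal electrodes.
- Table 1 lists the exclusion criteria. It has no numeric neutrophil or platelet limit. The nearest entry is "Severe coagulation disorders", which sets no count and does not concern neutrophils.

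**The concern.** One mL holds 1000 microlitres, so a count limit printed per mL is 1000 times lower than the same number per microlitre. At the printed unit the two limits are so low that almost no living candidate would fall below them, and they cannot work as a screen. Per microlitre, the same numbers are usable cut-offs. That contrast points to a slip in the unit and not to a deliberate choice.

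The sentence is an eligibility rule, not background. Candidates have had pelvic radiotherapy, some with a concurrent fluoropyrimidine (section 2.3). Those randomised to the treatment group then receive bleomycin and electrode insertion, and both groups go on to full-thickness local excision. The count limits are the only numeric guard in the article against entering these steps with low neutrophils or platelets, and feasibility/safety is a primary endpoint (section 2.1.1). As the text stands, a centre that applies the intended limits departs from the printed rule, and a centre that follows the printed rule has no effective count limit.

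**Working it through.** **Inputs, all from section 2.5.1**

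- Neutrophil limit: "An absolute neutrophil count below 1000/mL".
- Platelet limit: "a platelet count below 70,000/mL".

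The article derives neither limit from a calculation, so there is no planned figure to reproduce. The check is a unit conversion, with 1 mL = 1000 µL and 1 L = 1000 mL.

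**Step 1: the limits as printed**

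- Neutrophils: 1000 per mL ÷ 1000 = 1 per µL; 1000 per mL × 1000 = 10⁶ per L = 0.001 × 10⁹/L.
- Platelets: 70,000 per mL ÷ 1000 = 70 per µL; 70,000 per mL × 1000 = 7 × 10⁷ per L = 0.07 × 10⁹/L.

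**Step 2: the same numbers per microlitre**

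- Neutrophils: 1000 per µL × 10⁶ = 10⁹ per L = 1.0 × 10⁹/L.
- Platelets: 70,000 per µL × 10⁶ = 7 × 10¹⁰ per L = 70 × 10⁹/L.

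**Step 3: ratio and disputed range**

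| | Printed (per mL) | Same number per µL | Ratio | Counts on which the readings disagree |
|---|---|---|---|---|
| Neutrophils | 0.001 × 10⁹/L | 1.0 × 10⁹/L | 1000 | 0.001 to below 1.0 × 10⁹/L |
| Platelets | 0.07 × 10⁹/L | 70 × 10⁹/L | 1000 | 0.07 to below 70 × 10⁹/L |

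Example: a platelet count of 50 × 10⁹/L is 50,000 per µL, or 50,000,000 per mL. It is below 70,000 per µL, so the per-microlitre reading excludes the patient. It is far above 70,000 per mL, so the printed rule does not.

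**Step 4: how many patients this could touch**

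The article gives no rate of low counts 12 weeks after neoadjuvant therapy. Taking the share of candidates in the disputed ranges as 0%, 1% or 3% (an assumption), the number among 70 is:

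- 70 × 0.00 = 0
- 70 × 0.01 = 0.7
- 70 × 0.03 = 2.1

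**Step 5: could the unit be an artefact of text conversion?**

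The row of Table 1 that begins "Chronic renal dysfunction (creatinine> 150" continues with µmol/L, so the micro sign survives at least there. A micro sign that was simply dropped would also leave /L, whereas both count limits show a complete /mL. Replacement of the micro sign by the letter m remains possible, but nothing in the article shows that it happened.

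**The case against.** The strongest case on the other side is that this is an erratum and little more. The numbers 1000 and 70,000 are recognisable as per-microlitre cut-offs, and hardly any clinician would apply them per mL. The other safeguards still operate: a blood count is taken and seen, an INR above 1.5 excludes, severe coagulation disorders exclude, and the pre-anesthetic visit can exclude. The document is an article condensing a fuller protocol that is not shown, so the working protocol or case report form may carry the right unit. The intact micro sign in Table 1 shows only that one symbol was not lost; it does not rule out substitution in the body text. The 3% upper bound has no source in the article.

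Much of this stands. The practical effect is probably small, the intended unit is inferred, a conversion artefact cannot be wholly excluded, and the patient count is illustrative: it applies only if someone follows the literal unit. The point is also one of units, since no calculation in the plan is wrong.

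The conclusion survives all the same. The remaining safeguards supply no neutrophil or platelet number, and no other sentence in the article corrects these two. Leaving detail to a fuller protocol can explain a missing limit, but not a stated one that is wrong. If readers are expected to replace the printed unit with another, the printed unit needs correcting.

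**Conclusion.** The concern holds. As printed, both count limits are 1000 times lower than the same numbers per microlitre, and they would screen out practically nobody. The conversion is certain. That the intended unit was the microlitre is an inference, though a strong one, and the investigators need to confirm it.

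The likely consequence is modest: 0 to about 2 of 70 patients under the assumed 0% to 3% share, and fewer if centres already read the limits per microlitre. Sample size, power and the planned analyses do not depend on this sentence. It should be corrected because it is a safety-related entry rule that is wrong as written.

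**What to change.** Confirm the intended unit with the investigators, then restate both limits in section 2.5.1, presumably as neutrophils below 1000 per microlitre (1.0 × 10⁹/L) and platelets below 70,000 per microlitre (70 × 10⁹/L). Giving the value in × 10⁹/L as well removes any dependence on the micro sign. Check that the full protocol and the eligibility form carry the same unit. It would also help to repeat the two limits in Table 1, which now has no count.

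The cost is one unit changed twice in one sentence, with no additional procedure, patient or analysis.

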### 2.6. Assessment of Efficacy

The response of treatment in both the control arm and the treatment arm will be assessed with the histopathological TRG on tissue specimens after local excision.

The total number of cases with TRG 1 and 2 [28] will be recorded and the proportion of responses will be compared between the two groups.

If the histological examination documents the presence of carcinoma with at least one of the following characteristics: 1. ypT ≥ 2; 2. Positive margins; 3. TRG > 2; 4. Poorly differentiated form (G3), the local excision will be considered inadequate treatment and the patient will undergo TME.

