## 2. Trial Design

Seventy patients will be enrolled in a Phase II randomized controlled trial. The study will be developed in two stages. In the first step, 28 patients will be enrolled: 14 of these will receive ECT for four weeks after neo-adjuvant treatment and then local excision (treatment group) and 14 patients will receive neo-adjuvant treatment and then local excision (control group). Electrochemotherapy will be performed with the CLINIPORATOR™ and an intravenous dose of Bleomycin. If an increase of response rate is observed in the first stage and/or feasibility/safety is demonstrated, the second stage of the trial will be performed. In the second step, an additional 42 patients will be enrolled and treated. Trial design flow-chart is showed in Figure 1.

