### 2.8. Statistic Considerations

#### 2.8.1. Description of Sample Size Calculation and Planned Statistical Analyses

The sample size was determined by the Group-Sequential Superiority approach with a Margin Tests for the Difference of Two Proportions [36] using a complete response rate to the TRG after local excision as an endpoint. Sample size estimation has been carried out by using the superiority hypothesis in two independent parallel sample proportions [38,39,40,41,42]. According to the literature data, neoadjuvant chemo-radiotherapy treatment in LARC results in a complete response of 25% [43,44,45,46,47,48].

The proportion in the treatment group is assumed to be 0.25 under the null hypothesis and 0.50 under the alternative hypothesis. The proportion in the control group is assumed to be 0.25. The significance level of the one-sided test was targeted at 0.10 and the power at 80%.

An interim analysis will be conducted when 28 patients are enrolled (the percent of the sample size accumulated up to the corresponding look will be 40.0%). If a complete response rate to the TRG after local excision is noted in less than 25% of patients in the treatment group and/or feasibility/safety was not demonstrated, the study will be discontinued, otherwise a further 42 patients will be enrolled in the study.

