#### 2.8.2. Statistical Analysis

The treatment feasibility/safety of surgery following electrochemotherapy will be assessed considering the number of participants with compromised surgery following electrochemotherapy assessed by the R1 resection rate, circumferential resection margin (CRM) involvement, non mesorectal resection plane, and post-operative complications according to the Clavien-Dindo Classification. A surgical complications rate of 30–40% was reported in the literature for conventional neoadjuvant treatment followed by TME [37]. The evaluation of each arm will be performed at Visit 5 (12 weeks from ECT/8 weeks from LE).

Complete response rate (TRG 1 and 2), disease recurrence rates and percentages will be compared among the two groups. A one-sided Fisher exact test will be performed to test the differences between the groups. Differences will be considered significant at *p* < 0.10. A Chi square test will be performed to assess statistically significant differences among the groups for the categorical variable.

The time interval between the recruitment date and local disease progression will be represented using the time of treatment failure and median and minimum–maximum values will be considered.

The scores obtained by the QOL, pain and satisfaction questionnaires will be evaluated. Any serious adverse events and their intensity, according to the NCI-CTCAE classification (version 5.0), will be registered in the first two days post-procedure.

Mean ± standard deviation will be considered for normally distributed continuous variables while the median and interquartile range (IQR) will be presented for non-normally distributed continuous variables.

For continuous variables, the difference between follow-up values and baseline values will be tested by a 2-sided Student t-test or by a Mann–Whitney test while, for the categorical variables, the McNemar test and the marginal homogeneity test will be use [49,50].

Time to event outcomes will be analyzed using the Kaplan–Meier method and survival curves will be compared using the log-rank test.

Mixed effect regression models will be used to analyze longitudinal data by adjusting for proper covariates.

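### The primary feasibility measure does not count electrochemotherapy (ECT) left incomplete, or local excision (LE) not performed, unless an adverse event is recorded; the response proportion leaves the same patients undefined

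*Protocol article*

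**What the plan says.** Section 2.1.1 lists ECT feasibility/safety first among the primary endpoints, followed by the increase in complete response rate.

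- **Timing.** Under section 2.5.1 and Table 2, patients are randomised at Visit 1, up to one month before Day 0. ECT is given at Day 0 in the treatment arm, and LE follows at about Day 30 in both arms. Section 2.5.3 plans LE for every randomised patient. Section 2.4 allows for stopping: "Patients can decide to interrupt the treatment". It adds that those who withdraw are evaluated by study staff, but gives them no outcome.
- **Feasibility/safety.** Section 2.8.2 assesses it "considering the number of participants with compromised surgery following electrochemotherapy", through R1 rate, circumferential margin, resection plane and Clavien-Dindo complications. Section 2.7 adds AEs, with a collection at Visit 3 before LE. Section 2.8.3 acts on a 20% difference between arms in AE rate and surgical complication rate.
- **Response.** Under section 2.6, response "will be assessed with the histopathological TRG on tissue specimens after local excision"; the proportion with tumour regression grade (TRG) 1 or 2 is then compared between groups. The interim rule in 2.8.1 stops the trial if response is "noted in less than 25% of patients in the treatment group". The final test is a one-sided Fisher exact test at 0.10.

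**The concern.** Whether ECT can be carried out, and whether patients then reach excision, is the plain meaning of feasibility here. The stated measure does not ask either question. It looks at the quality and complications of surgery that took place, and the stopping rule adds AEs. A technical failure of ECT, or an excision refused or cancelled with no AE recorded, leaves no trace in either. ECT could then be declared feasible, and the second stage opened, despite such failures.

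The same patients are a problem for response. Without an LE specimen there is no TRG, and the article does not say how such a patient counts. Only the ECT arm has an additional invasive procedure and an intravenous cytotoxic between randomisation and LE, so losses could differ by arm and be related to outcome. With 14 patients per arm at the interim, one or two of them matter.

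**Working it through.** **1. The plan's own sample size.** Inputs from section 2.8.1: "The proportion in the treatment group is assumed to be 0.25 under the null hypothesis and 0.50 under the alternative hypothesis". The same section sets a control rate of 0.25, one-sided α = 0.10 and power 0.80. Section 2 gives 70 patients, and section 2.2 gives 1:1 allocation.

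n per arm = [1.2816·√(2·0.375·0.625) + 0.8416·√(0.25·0.75 + 0.50·0.50)]² / 0.25² = 32.9, so 33 per arm (66 in total).

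One interim look at 40% with O'Brien-Fleming-type spending (an assumption, since no spending function is stated) inflates this by 1.0085, giving 34 per arm (68). Normal-approximation power at 35 per arm is 81.8%. The stated 70 is therefore reproduced to within two patients. No allowance for loss before LE is stated.

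**2. Feasibility: what each kind of failure scores.**

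| ECT-arm patient | Surgical measures (2.8.2) | AE rate (2.7, 2.8.3) |
|---|---|---|
| Toxicity after ECT, LE cancelled | no score | counted |
| ECT not completed, no AE, uneventful LE | counted as uncompromised | not counted |
| LE not performed, no AE | no score | not counted |

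The first row is covered. The second and third are not.

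Illustration (the count of 3 is assumed): 3 of 14 ECT patients fall in the third row and no operated patient has a complication.
- Operated patients only: 0/11 − 0/14 = 0 points.
- Counted as failures over all randomised: 3/14 − 0/14 = 21.4 points.

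The 20% figure in 2.8.3 gives the scale. As written it applies to AE and surgical complication rates, not to failures of this kind.

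**3. Interim response rule (continue at 25% or more).**
- 14 counted: 3/14 = 21.4%, stop; 4 responders are needed.
- 13 counted: 3/13 = 23.1%, stop.
- 12 counted: 3/12 = 25.0%, continue.

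Two missing specimens are enough to reverse the decision. With a true response rate of 0.25 and loss unrelated to response, exact binomial enumeration gives different decisions from the two denominators in 3.9%, 10.7% and 21.4% of trials at assumed losses of 5%, 10% and 20%. At a true rate of 0.50 the figures are 0.9%, 2.9% and 8.4%.

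**4. Final test (one-sided Fisher, significant below 0.10).**
- 15/35 v 9/35: p = 0.104, not significant.
- 15/34 v 9/35, one ECT non-responder without a specimen: p = 0.088, significant.

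In the worst case, where only ECT-arm non-responders are lost and are then dropped, type I error (interim ignored) rises from 6.4% to 7.9%, 10.0%, 12.7% and 16.0% at losses of 5%, 10%, 15% and 20%. With all randomised patients counted it stays at 6.4%.

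**5. Cost of counting everyone.** A missing specimen counted as non-response turns a true rate p into p(1 − d) at loss d. Exact Fisher power at 35 per arm and d = 0 is 73.8%. At d = 5%:
- loss in the ECT arm only (0.475 v 0.25): 66.8%;
- the same loss in both arms (0.475 v 0.2375): 71.2%.

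At d = 10% the values are 59.1% and 68.7%; at d = 20% they are 43.0% and 63.2%.

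**The case against.** A reader might infer that both primary endpoints are scored only in patients who reach surgery. The article does not support that. Section 2.7 collects AEs at Visit 3 before LE, expressly to capture those due to ECT, and 2.8.3 puts the AE rate into the stopping rule. Toxicity that prevents excision is therefore seen.

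A reader might also infer that unexcised patients are dropped from the response rate, which inflates it, and that the interim rule contradicts section 2.6 by using another denominator. This is not supported either. Section 2.6 says how response is measured, not who is counted. The groups are defined by randomisation in 2.2, LE is planned for all in 2.5.3, and the interim rule uses the same TRG measure. Inflation is conditional on one reading of an undefined denominator.

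Three further points are fair. Analysis sets are often left to a fuller document. The final-test example sits at the boundary, and even worst-case one-sided loss takes the type I error past 10% only above about 10% loss. A smaller operated denominator can also raise a complication rate (3/12 v 3/14), so the direction is not fixed.

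What remains is that the article itself sets the feasibility measure and a numerical go/no-go rule. The measure as written misses feasibility failures without an AE. The 25% threshold cannot be applied to 14 patients until it is clear who is counted.

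**Conclusion.** The point holds for feasibility as a stated measure that is badly fixed: incomplete ECT, and LE not performed, score as failures only if an AE is recorded. It holds for response more narrowly, as an undefined denominator on which a small interim decision can turn.

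The size depends on losses that the article does not give. Three such patients in 14 would separate 0 points from 21.4. If unexcised patients were dropped, two missing ECT specimens could reverse the interim decision, and one could flip a final test near its boundary. With few or no losses the effect is small. The point should be settled before the interim analysis, but it does not invalidate the design.

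**What to change.** - **Sections 2.8.2 and 2.8.3.** Add to the feasibility measure the number of patients randomised to ECT in whom ECT was not completed or LE was not performed, over all randomised to ECT. State how this count enters the interim feasibility judgement. Report the number not reaching LE by arm.
- **Sections 2.6, 2.8.1 and 2.8.2.** Use all randomised patients by assigned arm as the denominator for the 25% rule and the final Fisher test. Count a patient without an LE specimen as a non-responder. Add a sensitivity analysis restricted to patients with a specimen.
- **Timing of LE.** Do not score it as a feasibility failure yet. Section 2.3.2 allows four weeks ±5 days after ECT, while section 2.5.3 and Table 2 give day 30 ±3. These must be reconciled first.

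The change takes a few sentences and no new data. Its costs are lower observed response rates and the loss of power shown in step 5, which is larger if would-be responders miss LE mainly in the ECT arm.
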